## Abstract

**Background:**

Brain-derived neurotrophic factor (BDNF) is essential for antidepressant treatment of major depressive disorder (MDD). Our repeated studies suggest that DNA methylation of a specific CpG site in the promoter region of exon IV of the BDNF gene (CpG -87) might be predictive of the efficacy of monoaminergic antidepressants such as selective serotonin reuptake inhibitors (SSRIs), serotonin-norepinephrine reuptake inhibitors (SNRIs), and others. This trial aims to evaluate whether knowing the biomarker is non-inferior to treatment-as-usual (TAU) regarding remission rates while exhibiting significantly fewer adverse events (AE).

**Methods:**

The BDNF trial is a prospective, randomized, rater-blinded diagnostic study conducted at five university hospitals in Germany. The study’s main hypothesis is that {1} knowing the methylation status of CpG -87 is non-inferior to not knowing it with respect to the remission rate while it significantly reduces the AE rate in patients experiencing at least one AE. The baseline assessment will occur upon hospitalization and a follow-up assessment on day 49 (± 3). A telephone follow-up will be conducted on day 70 (± 3). A total of 256 patients will be recruited, and methylation will be evaluated in all participants. They will be randomly assigned to either the marker or the TAU group. In the marker group, the methylation results will be shared with both the patient and their treating physician. In the TAU group, neither the patients nor their treating physicians will receive the marker status. The primary endpoints include the rate of patients achieving remission on day 49 (± 3), defined as a score of ≤ 10 on the Hamilton Depression Rating Scale (HDRS-24), and the occurrence of AE.

**Ethics and dissemination:**

The trial protocol has received approval from the Institutional Review Boards at the five participating universities. This trial holds significance in generating valuable data on a predictive biomarker for antidepressant treatment in patients with MDD. The findings will be shared with study participants, disseminated through professional society meetings, and published in peer-reviewed journals.

**Trial registration:**

German Clinical Trial Register DRKS00032503. Registered on 17 August 2023.

## Introduction

### Background and rationale {6a}

Currently, the treatment guidelines for moderate to severe major depressive disorder (MDD) recommend initiating treatment with an antidepressant drug (AD) [1–3]. However, extensive evidence suggests that only one-third of patients achieve complete symptom remission with the initial AD [4]. Additional treatment options, including switching antidepressants, combining different antidepressants, or adding lithium or antipsychotics, are commonly employed, and some have shown effectiveness [1–3]. Despite these treatment alternatives, approximately 40% of patients fail to respond adequately to AD treatments, resulting in a condition known as (pharmaco-)treatment-resistant depression (TRD). Additionally, 15–25% of patients even suffer from “difficult-to-treat depression” (DTD), which describes a depressive condition that “continues to cause significant burden despite usual treatment efforts” [5].

Treatment options for TRD/DTD encompass stimulation therapies such as electroconvulsive therapy (ECT) and innovative antidepressant agents like esketamine [6, 7]. These therapies have exhibited significant efficacy; however, they are typically administered at later stages of the illness, often following months or even years of inadequate treatment. Consequently, patients endure prolonged or chronic illness, leading to considerable personal and societal burden associated with the disease [8, 9]. Unfortunately, no routine diagnostic marker for stratifying or individualizing treatment decisions in MDD are available today.

Over the past few decades, there has been a significant advancement in the field of precision medicine. Although there is promising potential in the form of numerous biomarkers that require verification or falsification, precision psychiatry has yet to catch up [10, 11]. Precision psychiatry aims to integrate biological and environmental data to customize treatments [11]. In this context, the brain-derived neurotrophic factor (BDNF) plays a crucial role concerning antidepressant treatment for MDD. It is implicated in the pathophysiology of MDD as well as the mechanism of action of antidepressants [12–15]. BDNF exon IV has been extensively studied. It acts in regulating its expression through DNA methylation and histone modifications. It contains promoter elements and controls the production of activity-dependent BDNF [16]. We have consistently demonstrated that the DNA methylation of a specific CpG site within the promoter region of exon IV of the BDNF gene is crucial for the effectiveness of current monoaminergic antidepressant treatments, such as selective serotonin reuptake inhibitors (SSRIs), serotonin-norepinephrine reuptake inhibitors (SNRIs), and others [17–19].

Following an initial study conducted by Tadic et al. [17], in which a potential marker was identified in 44 depressed patients, we were able to replicate and validate this finding in a larger cohort of 199 severely depressed patients from the Early Medication Change study (EMC) [18]. In the EMC study, it was observed that patients exhibiting methylation at the CpG site -87 had an almost threefold higher likelihood of achieving remission than those with an unmethylated CpG site. These results were further supported by in vitro experiments, where the effective signaling of BDNF, stimulated by antidepressant incubation, was observed exclusively in constructs with a methylated BDNF exon IV promoter [17, 19]. Wang et al. [20] reported similar findings in a large sample of Chinese patients. However, there is a lack of prospective data regarding the potential of this marker to impact therapeutic decisions.

If our hypothesis that marker-guided treatment leads to reduced adverse events and medications without compromising treatment efficacy will be confirmed, incorporating this test before prescribing antidepressants could prevent unnecessary medication use and minimize the period of patient exposure to ineffective treatments, potentially saving several weeks or even months. This approach would enhance the likelihood of achieving remission from MDD within a shorter timeframe, thereby significantly alleviating patient suffering and reducing the direct and indirect costs associated with the disease.

Implementing a molecular test result as a determining factor for prescribing an antidepressant would represent a transformative shift in paradigm and pave the way for more precise and personalized treatment approaches for depression.

### Objectives {7}

The objective is to demonstrate that knowing the methylation status (marker group) compared to not knowing it (treatment-as-usual (TAU) group) does not result in a significantly lower remission rate and, at the same time, exhibits a statistically significant decrease in the rate of adverse events (AEs).

### Trial design {8}

The BDNF trial is a prospective, interventional, parallel-group, randomized, rater-blinded diagnostic trial conducted at five university hospitals in Germany. The study’s main hypothesis is to show that knowing the methylation status versus not knowing it does not lead to a significantly lower remission rate while significantly reducing AEs. Patient recruitment takes place within the more extensive multicenter cohort study “P4D—Personalized, Predictive, Precise & Preventive Medicine for Major Depression” (for further details, see: German Clinical Trial Register (DRKS) ID: DRKS00032215).

Within the P4D study, 1000 patients diagnosed with MDD undergo comprehensive assessments and deep phenotyping at two time points: upon hospitalization (baseline; BL (day 0–7)) and on day 49 (± 3) as a follow-up assessment (FU). Out of these 1000 patients, 256 eligible patients will be explicitly enrolled for the BDNF trial.

Upon inclusion in the BDNF trial, methylation on BDNF exon IV CpG -87 will be assessed in all patients, and they will be randomly assigned to one of two groups: the *marker group* or the *TAU group*. In the marker group, the test results will be communicated to the patient and their treating physician. Based on this information, treatment decisions will be made collaboratively using a shared decision-making approach. In the TAU group, neither the patients nor their treating physicians will be informed about the methylation status. Treatment decisions for this group will follow the national guidelines (refer to Fig. 1).

**Fig. 1 Fig1:**
[figure not shown]
The eligible participants (ITT (intention-to-treat) population) in the BDNF trial, recruited from the five university hospitals, will undergo testing for their BDNF CpG -87 methylation status. Baseline characteristics, including measures such as the Hamilton Depression Rating Scale (HDRS-24) and Montgomery–Åsberg Depression Rating Scale (MADRS) score, will also be collected. Subsequently, participants will be randomly assigned to one of two treatment arms: **a** the Marker group, where test results will be communicated to both participants and treating physicians, and the marker status will be considered in treatment decisions, or **b** TAU (treatment-as-usual) group, where no information about the test result will be provided to participants or physicians, and treatment decisions will be based on the national guidelines [1]

All participants of the BDNF trial will receive inpatient treatment for at least 49 days with weekly visits, and a follow-up assessment will be conducted on day 49 (± 3). Additionally, a follow-up by phone will be conducted on day 70 (± 3). Symptomatology as well as the occurrence of AEs will be assessed by raters who are blinded to the participants’ assigned groups. The criterion for the remission of depressive symptoms is indicated by an HDRS-24 sum score equal to or below 10. For evaluating AEs an extended version of the Dosage Record, and Treatment Emergent Side Effects scale (DOTES) is used weekly.

## Methods: participants, interventions, and outcomes

### Study setting {9}

A total of 256 patients will be recruited from five participating university hospitals in Germany: the Department of Psychiatry, Social Psychiatry, and Psychotherapy at Hannover Medical School (MHH; coordinating center), the Department of Psychiatry, Psychosomatics, and Psychotherapy at the University Hospital of Würzburg (UKW), the Department of Psychiatry and Psychotherapy at the University Hospital Schleswig–Holstein (UKSH), the Department of Psychiatry and Psychotherapy at University Medicine Greifswald, and the Department of Psychiatry, Psychosomatic Medicine, and Psychotherapy at the University Hospital Frankfurt (UKF). The study physicians within the P4D cohort will identify and enroll patients. Only patients in the inpatient setting will be eligible for inclusion in the trial.

### Eligibility criteria {10}

Before obtaining informed consent, the inclusion criteria are carefully reviewed and documented (Table 1). Patients who do not meet all the inclusion criteria or meet any exclusion criteria will be excluded from participating in the study. Patients who meet the criteria will be asked to sign a paper consent form, which will be stored at the respective study site.

**Table 1 Tab1:** Inclusion and exclusion criteria

**Inclusion criteria**	
Age	≥ 18– ≤ 70
Sex	Male, female, or diverse
Major depressive episode according to ICD-10 (F32.2–3, F33.2–3)	Single or recurrent episodes, as confirmed by the DIPS
Symptom severity	Severe (MADRS ≥ 34)
Modification in the therapeutic regimen is being considered	e.g., change of AD or change to neuromodulatory therapy
First MDD episode < 50 years	
Capacity for consent	
Written informed consent	
**Exclusion criteria**	
Acute suicidality	
Accommodation according to state law	(e.g., §16/17 Nds. PsychKG)
Persistent depressive disorder (PDD) (ICD-10: F34.1)	
(Lifetime) diagnoses of	Dementia, schizophrenia, schizoaffective disorder, bipolar disorder, substance addiction with currently necessary detoxification
Simultaneous participation in other clinical trials that are not conducted within the scope of the P4D project	

*Abbreviations: AD* antidepressant drug(s), *AE* adverse event, *ICD-10* 10th revision of the International Statistical Classification of Diseases and Related Health Problems, *MADRS* Montgomery–Åsberg Depression Rating Scale, *MDD* major depressive disorder, *Nds.* PsychKG Lower Saxony Law on Assistance and Protective Measures for the Mentally Ill

### Who will take informed consent? {26a}

The research team will notify eligible patients about the study. Either study physicians or study psychologists will discuss the study’s background and procedure with the patients. Information sheets and consent forms will be given to the patients, and the study physician or psychologist will secure written informed consent from each participant.

### Additional consent provisions for collection and use of participant data and biological specimens {26b}

After obtaining the signed informed consent, ethylenediaminetetraacetic acid (EDTA) whole-blood sample will be collected for DNA purification and testing of the BDNF CpG -87 marker in compliance with international standards and necessary quality assurance systems. After analysis of the marker, the remaining portion of the samples, blood as well as DNA, will be discarded. To date, no additional studies using the generated data and/or biological specimens are planned.

## Interventions

### Explanation for the choice of comparators {6b}

For evaluating the effect of knowing the BDNF -87 methylation status the best way forward is to compare the remission rate and the AE rate in the marker group (treating physicians and patients know the marker status) with a group of patients, who receive TAU (treating physicians and patients not knowing the marker status). In the TAU group, patients and physicians will select subsequent treatments based on national guidelines and the physician’s experience, following the common practices on the ward.

### Intervention description {11a}

For more details, please see the “Trial design {8}” section. The BDNF CpG -87 marker stands out as the initial predictive indicator for non-responsiveness to monoaminergic antidepressants, making it unique with no established gold standard or comparator. Within the study protocol, no specific treatment protocol is provided, allowing the marker to be tested under real-world conditions.

### Criteria for discontinuing or modifying allocated interventions {11b}

Given that there is no study drug intake or intervention involved, aside from the knowledge of the marker status, discontinuation of allocated interventions will not be required during the diagnostic trial.

### Strategies to improve adherence to interventions {11c}

In the current study, study nurses, physicians, and psychologists will monitor inpatients on a weekly basis until the follow-up period. Consequently, patients will benefit from additional attention and care from the study team to ensure adherence to the study protocol.

### Relevant concomitant care permitted or prohibited during the trial {11d}

This intervention occurs within a real-world setting, and as such, no concomitant care or interventions are excluded.

### Provisions for post-trial care {30}

No provisions for post-trial care are provided, as there is no anticipated risk of harm associated with the patient’s participation in the study. Nonetheless, patients are covered by insurance under an accident insurance policy.

#### Compensation

Participating patients are not receiving any form of compensation.

#### Patient and public involvement

Patient participation is a crucial component of the study as it allows the research consortium to address and respond to the needs and concerns of patients regarding the novel biomarker-based treatment approach. By involving patients, prejudices, and misconceptions can be thoroughly discussed and directly addressed during the recruitment process and communication of study findings. In the project’s initial year, the German Depression Foundation (GDF) will conduct a quantitative study to evaluate the beliefs, opinions, knowledge, barriers, and concerns surrounding the use of blood-based biomarkers to guide treatment decisions for depression. This assessment will encompass patients with MDD as well as the general population. The obtained results will serve as a basis for developing informative materials that will be provided to participating patients, as well as for guiding ongoing training for all participating medical doctors, focusing on essential considerations when offering the use of blood-based biomarkers. Through collaboration with the German Alliance Against Depression, the GDF will engage a Patient Advisory Board (PAB) that will be involved in all stages of the proposed study. The PAB’s responsibilities will include, among others, contributing to the design of the quantitative study, shaping information materials, discussing interim study findings, and reviewing public releases based on their expertise and lived experience. By participating in the project’s activities, patients will be enabled to engage in important processes related to their individual health and well-being. Active PAB members will also receive a small monetary allowance for their contribution, and their travel expenses will be reimbursed.

### Outcomes {12}

#### Primary outcome

Two co-primary endpoints are used for evaluating the predictive value of BDNF -87 methylation. The 1st co-primary endpoint is the rate of patients achieving remission during therapy, defined as a score of ≤ 10 on the Hamilton Depression Rating Scale (HDRS-24) on day 49 (± 3). The HDRS-24 is commonly used in clinical trials for depression and remission is considered the most relevant outcome for patients. Achieving remission indicates a higher likelihood of full recovery, improved quality of life, and reduced risk of experiencing a chronic-recurrent form of depression. This endpoint focuses on the absence of residual symptoms rather than just a partial response.

The 2nd co-primary endpoint is the rate of AEs. For evaluating AEs an extended version of the DOTES is used on a weekly basis. If a patient has at least one AE with an intensity of three within the time interval of 49 (± 3) days, it is counted for the co-primary endpoint.

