#### 2nd co-primary endpoint (AE rate)

In a meta-analysis conducted by [21], which examined the efficacy of SSRIs and the incidence of AEs based on placebo-controlled studies, the median AE rate was 0.8 in the treatment group. In this trial, it is assumed that knowing the marker status will result in a reduced use of antidepressants, leading to fewer AEs during pharmacotherapy. Conservatively, it is assumed that the AE rate will be half in the biomarker-negative group compared to the rate in patients treated with antidepressants (AE rate in antidepressant-treated patients: 0.8, AE rate in patients not treated with antidepressants: 0.4). Therefore, it is assumed that the AE rate in the marker group is 0.6, calculated as the mean of the expected AE rates stated. Since all MDD patients in the TAU group receive antidepressant treatment, an AE rate of 0.8 is assumed. A sample size of 218 achieves 90% power to detect a rate difference of − 0.20 (marker − TAU group) for the assumed AE rates, with a one-sided type I error of 2.5%.

To demonstrate the value of knowing the marker status for both co-primary endpoints with sufficient robustness, the final sample size was determined based on the 1st primary endpoint, which requires a larger sample size (*n* = 222 vs. *n* = 218). To compensate for potential treatment effect reduction due to study dropouts, the sample size is increased by 15% to ensure a conservative sample determination (*n* = 256). Sample size calculation was performed with nQuery 9.3.

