### Methods in analysis to handle protocol non-adherence and any statistical methods to handle missing data {20c}

In the event that patients choose to discharge themselves from the hospital before their scheduled follow-up visit, they will be requested to perform third-party assessments using the MADRS, HDRS-24, DOTES scales, and report their medication/treatment status on the day of discharge. Additionally, they will be queried about the feasibility of conducting a follow-up over the phone using the same set of questionnaires. However, if missing values occur in one of the two co-primary endpoints, they are addressed in the following way: Missing values in the 1st primary endpoint “Remission Rate” are defined as “Treatment Failures” and missing values for the endpoint “AE rate” are defined as having “Had at least one adverse event.”

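### The 90% power for the AE co-primary endpoint rests on AE rates with no stated intensity threshold, while the endpoint counts only AEs of intensity three

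*Protocol article*

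**What the plan says.** Outcomes {12} gives the only operational definition of the second co-primary endpoint. AEs are rated weekly on an extended DOTES, and the counting condition is "If a patient has at least one AE with an intensity of three" within 49 (± 3) days.

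Sample size {14}, in the part on the AE rate, draws its starting value from a meta-analysis described as covering "the efficacy of SSRIs and the incidence of AEs based on placebo-controlled studies". From it the plan reports that "the median AE rate was 0.8 in the treatment group". It then assumes half of this without antidepressants ("AE rate in patients not treated with antidepressants: 0.4") and averages the two: "it is assumed that the AE rate in the marker group is 0.6". TAU stays at 0.8. For these rates 218 patients are said to give 90% power at a one-sided 2.5% level.

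Two other places describe the event without a threshold. The abstract's main hypothesis says that knowing the marker "significantly reduces the AE rate in patients experiencing at least one AE". The missing-data rule in {20a} and {20c} treats a missing AE value as "Had at least one adverse event".

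**The concern.** The event to be tested carries an intensity threshold. The source rate, the halving and the averaging carry none, and no step translates one into the other. Within one population assessed in one way, patients with an intensity-three AE are a subset of patients with any AE, so a rate for the unrestricted event cannot simply be carried over.

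Much depends on this endpoint. {20a} requires both co-primary criteria to be met. {14} defends the 20-point non-inferiority margin for remission partly on the ground that a significant AE reduction is crucial to success. The two sample size requirements are also almost equal (222 and 218). If the AE rates are lower and the relative effect is the same, the AE endpoint determines the total sample size, not remission.

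**Working it through.** **Inputs from {14}.** TAU rate 0.8; marker rate (0.8 + 0.4)/2 = 0.6; biomarker-positive share 0.5; one-sided 2.5%; 90% power; 1:1 allocation; 218 patients for this endpoint, 222 before and 256 after the dropout allowance. **Not in the document:** any expected rate of intensity-three AEs. The TAU rates below 0.8 used here are assumptions.

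**Step 1: reproduce the plan's figure.** Pooled two-proportion formula, with p̄ the mean of the two rates:

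n per arm = [1.960·√(2p̄(1−p̄)) + 1.2816·√(p₁(1−p₁) + p₂(1−p₂))]² / (p₁−p₂)²

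For 0.8 and 0.6: p̄ = 0.7, √0.42 = 0.6481, √0.40 = 0.6325. So n = (1.2702 + 0.8105)² / 0.04 = 108.2, rounded up to 109 per arm, or 218 in total. Power at 109 per arm is 90.2%. The stated figure is correct for these rates.

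**Step 2: the relative effect in the plan.** 0.6/0.8 = 0.75, a 25% reduction overall. It arises from a halving in the biomarker-negative half and no change in the other half.

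**Step 3: power if the 25% relative reduction is unchanged.**

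Power = Φ{ [|p₁−p₂|·√n − 1.960·√(2p̄(1−p̄))] / √(p₁(1−p₁) + p₂(1−p₂)) }

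Example, 0.60 against 0.45 with n = 111: (1.5803 − 1.3842)/0.6982 = 0.281, and Φ(0.281) = 0.61.

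| Assumed TAU rate | Marker rate | Power, 111 per arm | Power, 128 per arm | Total N for 90% |
|---|---|---|---|---|
| 0.8 (plan) | 0.60 | 91% | 94% | 218 |
| 0.6 | 0.45 | 61% | 67% | 462 |
| 0.5 | 0.375 | 47% | 52% | 658 |
| 0.4 | 0.30 | 34% | 39% | 954 |
| 0.3 | 0.225 | 24% | 27% | 1444 |
| 0.2 | 0.15 | 16% | 18% | 2424 |

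The 128-per-arm column supposes that all 256 patients have an observed endpoint.

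**Step 4: power if the absolute difference of 0.20 persisted.**

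| TAU rate | Marker rate | Relative reduction | Power, 111 per arm |
|---|---|---|---|
| 0.6 | 0.4 | 33% | 85% |
| 0.5 | 0.3 | 40% | 87% |
| 0.4 | 0.2 | 50% | 91% |
| 0.3 | 0.1 | 67% | 97% |

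Every row needs more than the plan's 25%. Under the plan's own mechanism the whole difference comes from the biomarker-negative half, so it cannot exceed 0.5 × TAU rate. A difference of 0.20 therefore requires a TAU rate of at least 0.4, and at exactly 0.4 it requires no events at all in the biomarker-negative half of the marker group.

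**The case against.** The strongest reply is that the document does not establish a loss of power. It calls the 0.8 a median AE rate without the words any or overall, and the meta-analysis is not at hand. The trial's AE rate also need not resemble that of placebo-controlled SSRI studies: these are severely depressed inpatients, rated weekly on a scale extended to cover ECT, rTMS and esketamine effects, with free-text reporting besides. A reader might infer that the intensity-three rate must fall below 0.8. The subset argument supports that only within one population and one method of ascertainment, so the document makes it likely but not certain. Nor is a smaller absolute difference a necessary consequence; Step 4 shows that power largely holds if 0.20 survives. All of this stands, and it limits what can be said about size. It does not supply the missing link between the planning rates and the defined event.

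Two stronger readings are tempting and are not supported:

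- **The abstract and the imputation rule set up a second, rival endpoint.** Only {12} is an operational definition. The abstract sentence is a summary, and the imputation label can be read as counting the patient as having the event defined in {12}. This is loose wording to harmonise.
- **Imputation gives every dropout an AE of the highest intensity.** The article does not define the DOTES intensity scale, so three cannot be called its maximum. DOTES is collected weekly, at withdrawal or discharge, and by phone around day 49 where feasible, so leaving early need not mean a missing endpoint. The 15% in {14} is a sample size allowance, not a forecast of missing AE values.

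**Conclusion.** The point holds as a mismatch between the defined endpoint and its planning rates. The 90% power at 218 patients is computed correctly for 0.8 against 0.6, but nothing in the article shows that those rates describe patients with an AE of intensity three. The power for the endpoint to be tested is therefore not supported.

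The size is unknown from the document and depends on two assumptions: the intensity-three rate under TAU, and whether the relative or the absolute effect carries over. The relative version is closer to the plan's own reasoning, because {14} builds its effect by halving a rate. On that version even a TAU rate of 0.6 leaves about 61% power at 111 per arm. The shortfall would be small only if nearly all patients with an AE reach intensity three, or if the relative effect is clearly larger than the plan assumes. Since both co-primary criteria must be met, this should be settled before recruitment.

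**What to change.** In {14}, do one of the following:

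- justify 0.8 and 0.6 as rates of patients with at least one intensity-three AE;
- restate the planning rates for the intensity-three event, with their source, and give the resulting power, or the sample size if it changes;
- if 0.8 and 0.6 are meant for any AE, align the definition in {12} with them.

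Then use the same event wording in the abstract, {12}, {20a} and {20c}, including the label in the missing-data rule.

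The cost is amendment wording; the trial status section says recruitment has not started. If intensity three is kept, the stated power may become less favourable. Restoring 90% could require a much larger trial: 462 patients at a TAU rate of 0.6 with the 25% relative reduction, before any dropout allowance.
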